## Abstract

**Background:**

Post-traumatic headaches (PTH) are a common sequelae of traumatic brain injury (TBI) and greatly impact patient function and quality of life. Post-traumatic greater occipital neuralgia (GON) is a type of post-traumatic headache. Conventional treatment includes steroid/anesthetic injections which typically alleviate pain but have a short duration of effect. Platelet-rich plasma (PRP) is an emerging biological treatment for numerous degenerative disorders, including peripheral nerve disorders. The primary aim of this pilot study is to evaluate whether a randomized control trial of PRP for the treatment of GON in patients with post-traumatic headaches is feasible in regard to recruitment, adherence, retention, and adherence and adverse events. Exploratory aims include improvement in pain, function, and quality of life in patients with post-traumatic GON receiving PRP compared to steroid/anesthetic and normal saline injections.

**Methods:**

Thirty adults (over 18 years of age) with post-traumatic GON will be randomized into one of three groups: (1) autologous PRP injection, (2) steroid/anesthetic injection (standard care), or (3) placebo injection with normal saline. Injections will be performed to the greater occipital nerve under ultrasound guidance by a trained physician. Daily headache intensity and frequency data will be collected pre-injection and for the duration of the study period. Feasibility will be defined as greater than 30% recruitment, 70% completion of intervention, 70% retention, and less than 2 minor adverse events. Exploratory outcomes will be explored using the Headache Impact Test-6 (HIT-6, a valid and reliable 6-item questionnaire for assessment of the impact of headaches across different diagnostic groups of headaches) and the quality of life in following brain injury questionnaire (QOILIBRI).

**Discussion:**

This pilot study will be the first to evaluate the feasibility of PRP as a potential treatment of GON in patients with post-traumatic headache.

**Trial registration:**

ClinicalTrials.gov - NCT04051203 (registered August 9, 2019).

## Background

Traumatic brain injury (TBI) is a leading cause of death and disability [1]. Each year, an estimated 69 million people suffer from TBI worldwide, accounting for significant economic burden, with costs exceeding $76.5 billion ($85.1 in 2020 dollars) in the USA alone [2]. There are many medical sequelae following TBI that greatly impact an individual’s function and quality of life. Headache is one of the most common complaints, affecting up to 71% of TBI patients in the first year after injury, with headache symptoms persisting up to 10 years in some cases [3–5]. To date, the causal mechanisms of post-traumatic headache (PTH) have not been fully characterized, thereby limiting therapeutic targets.

PTH is a secondary headache disorder that can present with features of any primary headache disorder, and diagnostic criteria are defined by International Classification of Headache Disorders 3rd Edition (ICHD-3) [6]. Occipital neuralgia (ON) is a primary headache disorder, that can be seen commonly in the post-traumatic setting. ON is defined as unilateral or bilateral paroxysmal, shooting or stabbing pain in the distribution(s) of the greater, lesser, and/or third occipital nerves [6]. ON is most commonly unilateral (85%) and involves the greater occipital nerve in 90% of cases [7]. The etiology of greater occipital neuralgia (GON) is not fully understood, but damage and irritation along the course of the greater occipital nerve are believed to play a primary role in its pathogenesis [8]. Increased incidence following posterior head trauma, whiplash injury, and helmet use has been reported [9–11]. Patients with GON are typically treated with local greater occipital nerve blockade (cortisone and anesthetic), as it has the potential of being both diagnostic and therapeutic [6, 12].

Although greater occipital nerve blockade is effective in relieving headaches and associated pain, these effects are transient, with a mean duration of pain relief of just 1 month [13]. Furthermore, the risks and complications of repeated steroid injection such as weight gain, glycemic abnormalities, tissue necrosis, and hypothalamic-pituitary-adrenal axis suppression, make it less favorable as a long-term treatment [14, 15]. Other treatments described in the literature include systemic medications (i.e., NSAIDS, anti-depressants, anti-epileptics), botulinum toxin, pulsed radiofrequency ablation, occipital nerve stimulation, and surgical decompression [16, 17]. Unfortunately, these treatments have transient and widely variable success rates, highlighting the need for new and effective therapies.

Platelet-rich plasma (PRP) is an emerging biological treatment modality containing supraphysiologic concentrations of platelets, plasma, and associated growth factors [18]. PRP has garnered widespread interest as a safe and effective treatment modality in multiple fields, including orthopedics, sports medicine, ophthalmology, neurosurgery, and plastic surgery [19]. Given its efficacy in treating numerous degenerative and inflammatory conditions, PRP has recently been highlighted as a potential treatment for peripheral neuropathies [20, 21].

PRP’s anti-inflammatory and regenerative properties, safety profile, and longer duration of effect make it an attractive therapeutic modality over conventional steroid treatment in peripheral nerve disorders. PRP augments the biological repair process through several mechanisms. Specifically, it acts to encourage local angiogenesis, augment inflammation, inhibit catabolic cytokines, recruit local stem cells and fibroblasts, and induce local manufacturing of growth factors involved in tissue repair [21, 22].

Multiple animal and in vitro studies have demonstrated PRP’s ability to assist in remyelination, axonal regeneration, and functional neurologic recovery in models of peripheral nerve injury [20, 23–32]. There have been few in vivo studies of PRP in treatment of peripheral neuropathies with variable success rates [33–37]. One randomized controlled trial found significant pain reductions in 60 patients with carpal tunnel syndrome and improvement of multiple markers of nerve function which persisted to 6 months following a single PRP injection [20]. Another clinical trial found significant improvement in pain following perineural PRP injections in patients with diabetic polyneuropathy [30].

These findings are encouraging as they reveal new therapeutic avenues in the management of peripheral nerve disorders. To our knowledge, PRP has not been investigated as a treatment for GON. We believe that PRP’s physiology, demonstrated efficacy, and safety profile make it an exciting and novel strategy to treat this debilitating condition. This study will investigate the feasibility of a randomized control pilot study for the treatment of GON in patients with post-traumatic headache using PRP. This pilot trial will evaluate the ability to recruit patients, retain patients throughout the protocol and the feasibility of implementing randomization using PRP for the treatment of patients suffering with GON following TBI. Our specific objectives are the following:
Evaluate the feasibility of a randomized pilot study of PRP as a treatment for patients with GON and post-traumatic headache in terms of recruitment (greater than 30%), attendance (70% intervention appointment attendance), retention (greater than 70% complete protocol), and acceptability of the protocol.Evaluate the safety profile of PRP for the treatment of GON in patients with post-traumatic headaches with less than 2 minimal adverse events.Exploratory objectives include evaluating whether patients with GON and post-traumatic headaches receiving PRP have significantly decreases pain, improved function, and quality of life, compared to patients receiving cortisone/anesthetic and normal saline injections.

## Methods

### Study design

Prospective, randomized, controlled, double-blinded pilot trial evaluating the feasibility in relation to recruitment, retention, and acceptability of a single perineural PRP injection compared to that of steroid/anesthetic injection or injection with normal saline to the greater occipital nerve as a treatment for GON in patients following TBI. Flow through the study is portrayed in Fig. 1.

**Fig. 1 Fig1:**
[figure not shown]
Study design

### Study registration

The trial protocol is registered on ClinicalTrials.gov (NCT04051203). This study was registered at ClinicalTrials.gov on August 9, 2019; the study was open for enrollment at this time. This study protocol was prepared in accordance with the SPIRIT (Standard Protocol Items: Recommendations for Interventional Trials) guidelines for reporting clinical trials [38].

### Study setting and recruitment

Participants will be recruited primarily from the Calgary Brain Injury Program at the Foothills Medical Centre. Recruitment in this study will also be advertised at other Calgary-area neurology and sports medicine clinics. Once a participant is referred and has provided consent to contact, they will be contacted by a member of our research team. If they meet inclusion criteria at that time, an initial assessment will be scheduled and participants will complete a digital informed consent.

### Study participants

#### Inclusion criteria

Eligible participants will be males or females at least 18 years of age who suffer from post-traumatic headaches secondary to GON. Patients must fulfill the ICHD-3 criteria [6] for post-traumatic headache (Table 1) and for GON (Table 2) in establishing a diagnosis of post-traumatic GON. This diagnosis will be established by an experienced physiatrist and/or neurologist with extensive experience in headache and related disorders. To meet this criteria, participants must have experienced previous successful temporary relief with local anesthetic/steroid injection surrounding the greater occipital nerve in the past, but have not received local injection within the past 3 months. Pre-treatment numerical pain rating scale (NPRS) for daily headache intensity must be ≥ 4/10, with a headache frequency ≥ 10 days/month. Possible secondary causes of headache must be ruled out with a reasonable level of investigation prior to enrollment.

**Table 1 Tab1:** The International Classification of Headache Disorders 3^rd^ Edition (ICHD-3) diagnostic criteria for persistent headache attributed to traumatic injury to the head [6]

A.	Any headache fulfilling criteria C and D
B.	Traumatic injury to the head has occurred
C.	Headache is reported to have developed within 7 days after one of the following: 1. The injury to the head 2. Regaining consciousness following injury to the head 3. Discontinuation of medication(s) impairing ability to sense or report headache following injury to the head
D.	Headache persists for > 3 months after its onset
E.	Not better accounted for by another ICHD-3 diagnosis

**Table 2 Tab2:** The International Classification of Headache Disorders 3^rd^ Edition (ICHD-3) diagnostic criteria for occipital neuralgia [6]

A.	Unilateral or bilateral pain in the distribution(s) of the greater, lesser, and/or third occipital nerves and fulfilling criteria B-D
B.	Pain has at least two of the following three characteristics: 1. Recurring in paroxysmal attacks lasting from a few seconds to minutes 2. Severe in intensity 3. Shooting, stabbing, or sharp in quality
C.	Pain is associated with both of the following: 4. Dysesthesia and/or allodynia apparent during innocuous stimulation of the scalp and/or hair 5. Either or both of the following: a. Tenderness over the affected nerve branches b. Trigger points at the emergence of the greater occipital nerve or in the distribution of C2
D.	Pain is eased temporarily by local anesthetic block of the affected nerve(s)
E.	Not better accounted for by another ICHD-3 diagnosis

#### Exclusion criteria

Inability to provide informed consent; history of surgery in the occipital region; unstable psychiatric or medical condition; uncontrolled rheumatologic or inflammatory disorders; widespread neurologic disorders (e.g., MS); fibromyalgia/chronic fatigue syndrome; coagulopathy; immunosuppression; active cancer; herpes zoster infection in last 6 months; pregnancy; steroid injection to the greater or lesser occipital nerve infiltration in past 3 months.

### Blinding and randomization

Each participant will be randomized following screening and enrollment in the study. Participants will be randomized (via sealed envelope) by a blinded research assistant in a 1:1 fashion to one of three treatment arms: (1) autologous PRP injection, (2) steroid/anesthetic injection (standard care), or (3) placebo injection with normal saline. All patients will undergo 60 mL blood draw on their scheduled day of injection. Whole blood samples will be prepared in the PRP group only; otherwise, they will be discarded appropriately. Syringes (3 mL each) will be prepared by a research assistant and will be covered in an opaque tape so the physician providing the injection is blinded to the type of injectate. The physician will fill out a questionnaire at the time of injection indicating their best guess of the syringe contents, which will be evaluated afterwards, to ensure adequate blinding. Unblinding will occur only in extraordinary circumstances if knowledge of the actual treatment received is deemed essential to providing further patient care.

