#### Platelet-rich plasma

PRP will be prepared using the “Arthrex Angel System,” which is a fully automated PRP preparation machine. Sixty milliliters of blood will be drawn from the antecubital vein and processed via centrifugation. Five milliliters of sodium citrate will be added to the syringe prior to blood draw to prevent coagulation. Samples will be centrifuged as per manufacturer instructions, yielding 5 mL of PRP. For quality testing, 1 mL of PRP will be sent to the lab for analysis of platelet and leukocyte count, as compared to the patients’ whole blood. The remaining 4 mL of PRP will be divided into two syringes and 2 mL will be injected per symptomatic side.

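### Only PRP blood is processed and no described step equalises the wait between blood draw and injection, so a longer wait could signal PRP versus non-PRP and the universal draw may protect the blind only in part

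*Protocol article*

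**What the plan says.** The Study design section describes a "Prospective, randomized, controlled, double-blinded pilot trial", and the Methods paragraph of the abstract gives the size: "Thirty adults (over 18 years of age) with post-traumatic GON will be randomized into one of three groups". Allocation is equal across PRP, steroid/anesthetic and saline.

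The Blinding and randomization section sets out three safeguards:
- a blood draw in every arm: "All patients will undergo 60 mL blood draw on their scheduled day of injection";
- syringes that are "covered in an opaque tape so the physician providing the injection is blinded to the type of injectate";
- a questionnaire on which the physician records a guess of the syringe contents at the time of injection.

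The same section then states how the blood is handled: "Whole blood samples will be prepared in the PRP group only; otherwise, they will be discarded appropriately".

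The Platelet-rich plasma section describes what follows in that arm: "Sixty milliliters of blood will be drawn from the antecubital vein and processed via centrifugation", and "Samples will be centrifuged as per manufacturer instructions, yielding 5 mL of PRP". One millilitre goes for laboratory testing and the other four are split between two syringes. The Steroid/anesthetic and Normal saline sections list contents that do not come from the participant's blood.

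The article gives no centrifugation time, no draw-to-injection interval for any arm, and no matched wait.

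**The concern.** The article gives the draw no use in the two non-PRP arms, so its natural purpose there is concealment, although this is inferred from the section heading and not stated. A draw taken for concealment works fully only if what follows it also looks the same. Here a PRP injection cannot go ahead until the blood has been processed, and the other two have nothing to wait for. The tape hides what is in the syringe, not how long it took to arrive.

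Two things make this worth closing. First, pain ratings, headache diaries, HIT-6 and quality of life are all participant-reported, and the exploratory contrasts set PRP against steroid and against placebo. A cue separating PRP from non-PRP falls on exactly those contrasts. Second, the Primary outcomes section says the pilot is to inform a larger double-blinded trial, so a gap in the blinding procedure could carry over into that trial.

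**Working it through.** The plan states no figure on this point, so there is none to reproduce. The check has two parts.

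**1. The steps between draw and injection, side by side**

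| Step on injection day | PRP | Steroid/anesthetic | Saline |
|---|---|---|---|
| 60 mL draw | yes | yes | yes |
| Centrifugation | yes | no, blood discarded | no, blood discarded |
| Filling of syringes depends on the blood | yes | no | no |
| Opaque tape | yes | yes | yes |
| Stated wait before release | none | none | none |

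Let T be the time to process the blood and fill the PRP syringes, and H any common minimum wait before release, both counted from the draw. Ignoring the short time to fill a non-PRP syringe:
- wait in the PRP arm = max(T, H);
- wait in the other arms = H;
- difference = max(T − H, 0).

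With no common wait (H = 0) the difference is the whole of T. With H at least as long as T it is zero. The article gives neither T nor H. The direction is therefore fixed (PRP is never the shorter wait), but the size is not. The steroid and saline columns are identical, so the wait carries no information between those two arms.

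**2. What a leak would do to the planned physician guess (illustration)**

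Inputs from the article: 30 participants in 3 equal arms, so 30/3 = 10 on PRP and 20 not. Assumptions: all 30 are injected; the physician chooses among three contents; guesses are independent; and in a share q of sessions the wait discloses PRP versus non-PRP, the guess otherwise being random. The documents give no q, so the full range is shown.

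- Chance of a correct guess without disclosure: 1/3.
- With disclosure: PRP is always identified, and steroid versus saline remains a coin toss: 1/3 × 1 + 2/3 × 1/2 = 2/3.
- Overall: p = (1 − q)/3 + q × 2/3 = (1 + q)/3.

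| q | p | Expected correct of 30 |
|---|---|---|
| 0 | 0.333 | 10.0 |
| 0.25 | 0.417 | 12.5 |
| 0.50 | 0.500 | 15.0 |
| 0.75 | 0.583 | 17.5 |
| 1 | 0.667 | 20.0 |

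Take 15 or more correct of 30 as the signal. The exact binomial probability is 0.044 under pure chance, 0.57 at q = 0.5 and 0.98 at q = 1. The questionnaire would very probably show a full leak to the physician but would miss a half leak about 43% of the time (1 − 0.57). It does not measure what the participant has inferred.

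**The case against.** The strongest reply is that this is silence, not error. The article does not say that non-PRP participants are injected sooner; a common wait is compatible with every sentence; and the release time of a syringe is an operational detail that a condensed article may leave to the full protocol. That stands, and it is why no size can be attached to the leak. It does not remove the point: the article lists its blinding steps, states that blood is handled differently by arm, and none of those steps covers the resulting delay.

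A reader might infer more: that the wait reveals the arm in nearly every PRP participant, is seen by both participant and physician, and makes the universal draw useless. The documents do not support this.
- No times are given, so neither a difference nor its visibility can be established.
- The physician is not said to attend the draw or to know when it took place.
- Each participant has one injection session and no second wait to compare with. Decoding it requires knowing how long PRP takes and that other samples are not processed, and the article does not say that participants are told either.
- At most the wait separates PRP from non-PRP.
- Drawing blood from everyone removes the plainest cue, draw versus no draw.

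It is also fair that efficacy is exploratory here, that the article itself asks for cautious interpretation, and that detecting a leak is a proper function of a pilot. The illustration shows, however, that the planned check is weak against a partial leak. Finally, equal waits would not remove every cue: the steroid injectate contains lidocaine, and eligibility requires previous relief from an anesthetic/steroid injection. That limits what the fix achieves but does not argue against it.

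**Conclusion.** The point holds as an inexpensive improvement to the blinding procedure, not as a demonstrated failure of the blind. As described, PRP injections have a preparation step that the other two arms lack, and no described safeguard equalises the wait that follows from it. The universal draw may then protect the blind only in part, for PRP versus non-PRP: for the participant in any case, and for the physician if aware of the draw time.

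The size is unknown. It ranges from nil, if a common wait is already in use, to disclosure of PRP versus non-PRP in every session, where expected correct physician guesses would rise from 10 to 20 of 30. The upper end assumes that no common wait is used and that the wait is noticed and correctly interpreted.

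**What to change.** In the Blinding and randomization section, set one fixed interval from blood draw to injection for all three arms, long enough for PRP preparation to finish within it. State that the taped syringes are released only when the interval has elapsed. If a common wait is already used, a sentence saying so closes this part of the point.

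Record the draw and injection times for each participant, and report the interval by arm alongside the blinding-guess data. This lets readers see whether the waits were in fact equal and sets the guesses in context.

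The cost is extra waiting on injection day for about 20 non-PRP participants, plus two recorded times per session. No extra blood and no sham centrifuge run is needed, and no treatment or sample size changes.

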### Interventions

Injections will be prepared as stated below. Patients will be asked to complete a numeric pain rating scale (NPRS) immediately pre- and post-injection. Patients will be asked to refrain from use of anti-inflammatory medications for 2 weeks prior to the injection and for 2 weeks following the injection due to the possible inhibitory effect on the action of PRP. Two 3 mL syringes with 2 mL of injectate (PRP, steroid/anesthetic, or normal saline) will be prepared for each participant. Patients will be assessed at the time of injection and will receive a single injection, if experiencing unilateral symptoms only, or two injections to each greater occipital nerve, if symptoms are bilateral. Patients will be monitored for 30 min following injection for any immediate adverse reactions, such as local reaction, increased pain intensity, anaphylaxis, nausea, or dizziness.

#### Platelet-rich plasma

PRP will be prepared using the “Arthrex Angel System,” which is a fully automated PRP preparation machine. Sixty milliliters of blood will be drawn from the antecubital vein and processed via centrifugation. Five milliliters of sodium citrate will be added to the syringe prior to blood draw to prevent coagulation. Samples will be centrifuged as per manufacturer instructions, yielding 5 mL of PRP. For quality testing, 1 mL of PRP will be sent to the lab for analysis of platelet and leukocyte count, as compared to the patients’ whole blood. The remaining 4 mL of PRP will be divided into two syringes and 2 mL will be injected per symptomatic side.

